#### Analyses of secondary aims

We plan on examining the effects of exercise motivation, dietary motivation, social support and outcomes expectancies on weight change. We will also explore whether ethnicity, gender, mental health diagnostic group, medication type, and metabolic syndrome moderates the treatment effect on weight change. Furthermore, we will examine whether there was an effect of the intervention on patient reported outcomes including body image (Body Weight, Image and Self-Esteem Evaluation Questionnaire - B-WISE), psychiatric symptoms (Colorado Symptom Index - CSI), quality of life (Wisconsin Quality of Life Index - W-QLI), health-related self-efficacy (Patient Activation Measure - PAM), health (SF-36 general health subscale), and functional status (Behavior and Symptom Identification Scale - BASIS-24). Finally, we will evaluate whether dose, defined as the number of intervention sessions and number of telephone and email contacts, is related to change in the outcomes across time among participants who received the intervention.

#### Power analysis of primary aims

We used data from PREMIER DASH diet arm results [30] to estimate power for repeated measures analysis of variance for change in weight. We used repeated measures ANOVA given the lack of well-established methods for estimating power using GEE. Data were available for change at 6 and 18 months. Because reported means and standard deviations were based on completers alone, we adjusted for attrition in our power analyses (although primary analyses will be intent-to-treat). PREMIER reported a 5.9% decrease in weight at 6 months for the DASH diet group and a 1.6% decrease for control (advice only). With an initial total sample size of 280, a 10% (worst case) attrition rate at six months, and alpha level of .05, we have power of .96 to detect a significant group-by-time interaction at 6 months. Using the 18-month values (−1.6% for advice only, -4.4% for DASH) as a conservative estimate for weight change at 12 months, we have power of .87 for the group-by-time interaction term for weight (assuming a 15% worst-case attrition rate). To estimate power at 24 months, we assumed the same rate of weight gain in the DASH group and weight loss from 6 to 18 months in the UC group, consistent with PREMIER. For a 3.6% decrease from baseline in the DASH group and 1.8% decrease for UC at 24 months, we have power of .80 to detect a significant group-by-time interaction at 24 months, assuming 20% attrition. Power for waist circumference, fasting insulin, and insulin sensitivity were based on data reported by Ard [31]. Power for total cholesterol, LDL, and HDL were based on data reported by Obarzanek [64]. Only baseline and 6-month means were available for these variables, so we have computed power to detect a significant group-by-time interaction at 6 months only. For all variables, power exceeds .95 to detect the group-by-time interaction.

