**Discussion:**

The STRIDE study is based on a modified version of the PREMIER comprehensive lifestyle intervention, DASH diet arm. STRIDE has successfully enrolled 200 individuals with serious mental illness in community-based settings. Baseline characteristics present a population at high risk for obesity-related negative health outcomes and demonstrate the need for evidence-based interventions to reduce these risks.

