### Baseline characteristics

A total of 200 individuals with serious mental illnesses were randomized to one of the treatment arms. Two participants became ineligible after randomization, one due to pregnancy and one due to an unspecified but serious health problem that caused repeated vomiting and resulted in a significant weight loss. At baseline (Table 2), participant diagnoses were affective psychosis (38%), bipolar disorder (32%), schizophrenia spectrum disorders (29%) and PTSD (2%). Participants were taking an average of 3.2 psychiatric medications and 91% were taking an atypical antipsychotic medication. Study participants were an average age of 47.1 (SD = 10.7) years old. Thirty percent were currently working and 35% reported being disabled. About 31% of the sample had a high school diploma, GED or less, and 43% were married or living with a partner.

**Table 2 T2:** Baseline characteristics of the study participants (N = 200)

**Characteristic**	**n (%)**^ **1** ^
Inclusion diagnosis	
Affective psychosis	75 (38)
Bipolar disorder	63 (32)
Schizophrenia spectrum disorder	58 (29)
Post-traumatic stress disorder	4 (2)
Gender	
Male	56 (28)
Female	144 (72)
Race^2^	
White	171 (88)
Non-white	24 (12)
Hispanic ethnicity	4 (2)
Education	
Less than high school	15 (8)
High school graduate/GED	46 (23)
Some college/technical school	87 (44)
College graduate	37 (19)
Post graduate	15 (8)
Marital status	
Never married	57 (29)
Widowed/Divorced/Separated	57 (29)
Married	69 (34)
Living with partner	17 (9)
Annual household income	
$0 - $9,999	54 (28)
$10,000 - $29,999	58 (30)
$30,000 – $49,999	34 (17)
$50,000 or higher	49 (25)
Number of people supported by income, mean (SD)	2.0 (1.3)
Employment status	
Currently working	59 (30)
Disabled	71 (36)
Retired, unemployed, student, homemaker, temporarily laid off, or other	70 (35)
Atypical antipsychotic medication use	182 (91)
Medications taken that affect weight	
≥1 that cause slight/moderate weight loss	77 (39)
≥1 that do not affect weight	168 (84)
≥1 that cause slight/moderate weight gain	21 (11)
≥1 that cause severe weight gain	128 (64)
Mood stabilizer medication use	97 (49)
Anti-depressant medication use	33 (17)
Smoked in the past year	65 (33)
Self-reported diabetes diagnosis	
No	145 (73)
Yes	48 (24)
Don’t know	7 (4)
Self-reported hypertension diagnosis	
No	114 (57)
Yes	70 (35)
Don’t know	15 (8)

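### The power statement rests on 280 participants, but 200 were randomised; at 200 the 12- and 24-month powers of .87 and .80 become about .74 and .66

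*Protocol article*

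**What the plan says.** The protocol article's section on power for the primary aims gives one sample size, in its 6-month sentence: "With an initial total sample size of 280, a 10% (worst case) attrition rate at six months, and alpha level of .05". With that number it claims power of .96 at 6 months for a weight loss of 5.9% against 1.6%. For 12 months it writes "Using the 18-month values (−1.6% for advice only, -4.4% for DASH) as a conservative estimate for weight change at 12 months" and claims .87 with 15% attrition. For 24 months it assumes losses of 3.6% and 1.8% and concludes "we have power of .80 to detect a significant group-by-time interaction at 24 months, assuming 20% attrition". It closes by putting power above .95 at 6 months for waist circumference, insulin, insulin sensitivity and lipids.

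The Baseline characteristics section states: "A total of 200 individuals with serious mental illnesses were randomized to one of the treatment arms". It adds that "Two participants became ineligible after randomization", which leaves 198. The abstract's Discussion treats enrolment as complete: "STRIDE has successfully enrolled 200 individuals with serious mental illness in community-based settings". Table 2 also has N = 200.

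**The concern.** The power claims are in the present tense, in an article that already reports completed enrolment and baseline data. Nothing labels 280 as a superseded target, mentions the 80 missing participants or restates power. Both the abstract and the main Discussion describe recruitment favourably.

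The primary aims cover 6, 12 and 24 months, so the later visits matter. A reader who relies on the printed figures would take a non-significant 12- or 24-month result as coming from a trial with a type II error of .13 or .20 against the planned effects. At 200 participants, on the plan's own assumptions, these errors are about .26 and .34.

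**Working it through.** **Inputs from the power section.** N = 280; alpha .05 (sidedness not stated, two-sided assumed); power .96, .87 and .80; attrition 10%, 15% and 20%; differences in weight change of 5.9 − 1.6 = 4.3, 4.4 − 1.6 = 2.8 and 3.6 − 1.8 = 1.8 percentage points. **From Baseline characteristics:** 200 randomised. **Not given:** SD of weight change, within-person correlation and allocation ratio.

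**The plan's own figures.** They cannot be reproduced from first principles without an SD and a correlation. They can be rescaled. With effect, attrition rate, alpha and variability fixed, the noncentrality is proportional to √N, so the unknown SD, correlation and allocation ratio cancel.

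- Noncentrality at 280: δ₂₈₀ = 1.96 + z(power)
- Noncentrality at 200: δ₂₀₀ = δ₂₈₀ × √(200/280) = δ₂₈₀ × 0.845
- Power at 200: Φ(δ₂₀₀ − 1.96)

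| Visit | Stated power | δ₂₈₀ | δ₂₀₀ | Power at 200 |
|---|---|---|---|---|
| 6 months | .96 | 3.71 | 3.14 | .88 |
| 12 months | .87 | 3.09 | 2.61 | .74 |
| 24 months | .80 | 2.80 | 2.37 | .66 |

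For an outcome with power of exactly .95 at 280: 3.605 × 0.845 = 3.047, and Φ(3.047 − 1.96) = .86.

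**Sensitivity to what is unstated**, in the order 6, 12 and 24 months:

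- N = 198: .877, .737, .654.
- One-sided alpha, N = 200: .890, .757, .676.
- Noncentral F with 1 to 3 numerator degrees of freedom, N = 200: .868–.879, .724–.740, .640–.657.
- N = 200 with no attrition, so that δ₂₈₀ is multiplied by √(200/252), √(200/238) and √(200/224): .911, .808, .754.

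**Detectable differences.** This step needs a further assumption: a simple two-group comparison of change at each visit with equal arms. The detectable difference at 80% power is then the planned difference × 2.80/δ₂₀₀: 4.3 × 2.80/3.14 = 3.8; 2.8 × 2.80/2.61 = 3.0; 1.8 × 2.80/2.37 = 2.1 points. At 12 and 24 months these exceed the planned 2.8 and 1.8.

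**Check on that assumption.** The implied SD is difference × √(n/2)/δ₂₈₀, with n = 126, 119 and 112 per arm. It is 4.3 × 7.94/3.71 = 9.2, 2.8 × 7.71/3.09 = 7.0 and 1.8 × 7.48/2.80 = 4.8 points. No single SD yields all three stated powers. With an SD of 7.0, the 24-month power would be .49 at N = 280 and .37 at N = 200. Either the repeated measures calculation used assumptions not shown, or the stated powers do not fit together.

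**The case against.** The strongest reply is that this is a planning figure that was not updated, and no calculation in the section is shown to be wrong. The 200 is openly reported, recruitment is closed, and no endpoint or model changes. This limits the consequence, but the text does not call the figures historical and presents them as the trial's power.

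Three narrower points have force:

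- The 280 appears only in the 6-month sentence. Carrying it to the later visits and other outcomes is an inference. It is the natural one, since no other number appears and the later weight sentences change only effect and attrition.
- The replacement powers are conditional on the printed ones, and the implied SDs that nearly halve from 6 to 24 months show that a simple change model may not match the calculation done. The rescaled powers do not need that model; the detectable differences do and are illustrative.
- Attrition could be lower than assumed; the 10% and 15% are labelled worst-case. With no attrition at all, however, every power is still below its stated value.

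Nothing in the article says a null result will be taken as proof of no effect. That risk lies in how readers use the figures.

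**Conclusion.** The concern holds. The printed power belongs to a trial of 280, and this trial has 200. Holding the plan's effects, attrition rates and alpha (two-sided), and taking the stated powers as correct at 280, power for weight is about .88 at 6 months, .74 at 12 and .66 at 24. Across the variants that keep the stated attrition, 12 months lies within about .72–.76 and 24 months within about .64–.68. The floor for the other outcomes moves from .95 to about .86. Six-month power for weight remains reasonable, and type I error is unaffected. The true 24-month figure could be lower than .66 if the variability of weight change does not shrink over time as the stated powers imply.

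**What to change.** Rewrite the power paragraph to say that 280 was the planned and 200 the achieved number. Recompute power for 200 at the stated attrition rates, from the SDs and within-person correlation actually used, and print those inputs. Expect about .88, .74 and .66 for weight if the original figures were right. Give the detectable difference at each visit, with the model behind it, and the recomputed 6-month power for waist circumference, insulin, insulin sensitivity and lipids. State the sample size behind each figure and explain how one set of assumptions yields all three weight powers. Add that non-significant 12- and 24-month results are to be interpreted from their confidence intervals.

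The cost is a few lines of text, one rerun of the power calculation and a less favourable power statement. No further recruitment or change to the analysis is needed.

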#### Implementation and process evaluations

The implementation evaluation included observations of organizational and other facilitators and barriers to implementation; results of this evaluation are described elsewhere [25]. Fidelity assessments documented adherence to the intervention protocol and thus will allow examination of implementation differences across groups. Assessment of intervention fidelity includes both qualitative and quantitative measures.

The study design also included a process evaluation component, which sought to understand participants’ feelings toward, and responses to, the different elements of the intervention and to lifestyle change more generally. Semi-structured interviews lasting approximately 30 minutes were conducted with participants at 3- (n = 38), 9- (n = 35), and 18-months (n = 29) following randomization. Interviewers asked about barriers and facilitators of dietary and exercise changes. Of these, 76% (n = 78) were conducted with intervention participants and 24% (n = 24) with control participants. Interviews were transcribed verbatim and coded using Atlas.ti. Analyses will identify themes related to lifestyle improvements across participants; check coding will assess inter-coder reliability.

#### Cost-utility analysis

The study was designed to conduct a cost-utility analysis and includes estimates of the direct costs, per participant, of implementing the intervention. Relevant costs for these analyses will include the resources necessary to deliver the intervention and the change in care costs incurred by the organization that derive from the intervention. We have included the EQ-5D [65], a brief, self-administered, health-related quality of life measure that assesses mobility, self-care, usual activities, pain/discomfort, and anxiety/depression dimensions. Response patterns yield 243 unique health states, and are commonly used to generate a composite score or index reflecting the preference value (utility) associated with a given health state. We will calculate incremental cost-effectiveness ratios for each intermediate trial outcome, and will further report such a ratio for the improvement in mean EQ-5D scores between the intervention and control groups.

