**Methods/design:**

The STRIDE study is a multi-site, parallel, two-arm randomized controlled translational trial. Participants were recruited from community mental health clinics and an integrated not-for-profit health system. Participants were randomized either to usual care or to a 12-month intervention that consisted of: 1) weekly group participation for six months covering topics on nutrition, physical activity and lifestyle changes; 2) monthly group participation for an additional six month maintenance period; and 3) individual monthly contacts from intervention group facilitators during the second six month phase. All participants are assessed at baseline, 6, 12, and 24 months post-enrollment. Process and implementation evaluations are included and the study design includes a cost-utility analysis. Participants include 200 individuals with serious mental illness with an average age of 47.1 years, a mean body-mass index of 38.3 kg/m^2^ and taking an average of 3.2 psychiatric medications at baseline. Baseline physiological measures included mean blood pressure (SBP/DBP) measurements of 119.2 (SD = 14.7)/79.4 (SD = 10.1); 35% reported a hypertension diagnosis and 11% took antihypertensive medications. Average lipid levels (mg/dL) were: a) triglycerides 188.0 (SD = 138.6), ranged from 43 to 1145; b) LDL 101.4 (SD = 32.9) and ranged from 17 to 185; c) HDL 45.8 (SD = 12.7) and ranged from 22 to 89; and d) total cholesterol 181.6 (SD = 39.7) and ranged from 50 to 324. Average fasting glucose levels were 108.9 (SD = 32.5) and ranged from 24 to 289. Average fasting insulin levels were 13.0 (SD=11.9) and ranged from 2 to 99.

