### Assessment data collection and measurement

Intervention and usual care groups were assessed at baseline, 6, 12, and 24 months. Laboratory, physiological and anthropometric measures were obtained at each assessment and included: 1) height in meters measured to the nearest 0.1 cm (baseline only), 2) weight in kilograms measured to the nearest 0.1 kg (body mass index was calculated as the Quetelet index [kg/m^2^]), 3) waist circumference, measured over participants’ underwear using inelastic tape at the narrowest part of torso and measured in a horizontal plane without compressing the skin, and 4) blood pressure, measured while participants were seated with legs uncrossed and without talking after a 5-minute rest period, and then again after an additional 30 second rest period. Blood was drawn and all lab panels were collected after an overnight (8–12 hour) fast. Tests included: 5) fasting insulin, 6) fasting plasma glucose, 7) fasting triglycerides, and 8) fasting cholesterol (total, HDL, LDL).

We followed the National Cholesterol Education Program (NCEP) guidelines [45] and defined metabolic syndrome as: Individuals with 3 or more of the following risk factors: a) waist circumference greater than 102 centimeters in men or 88 centimeters in women; b) triglycerides plasma level of 150 mg/dL or greater; c) HDL-cholesterol plasma level less than 40 mg/dL for men or less than 50 mg/dL for women (or taking cholesterol-lowering medications); d) blood pressure of 130/85 mm Hg or greater (or taking antihypertensive medications), and/or e) fasting glucose greater than or equal to 110 mg/dL (or taking glucose lowering medications).

To assess insulin resistance, we calculated the Homeostasis Model Assessment Index for Insulin Resistance (HOMA-IR) as follows: fasting glucose [mmol/L] × fasting insulin [μU/mL]/22.5. This index correlates very highly with the gold standard hyperinsulinemic euglycemic clamp [46].

We included several self-reported measures to describe participants and assess health and functional status and medication use. These measures are shown in Table 1.

**Table 1 T1:** STRIDE measures and data collection schedule

	**BL**	**6 month**	**12 month**	**24 month**

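### The cost-utility ratio divides cost by a difference in mean EQ-5D score, which carries no duration, so it is not cost per QALY; Table 1 also omits EQ-5D

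*Protocol article*

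**What the plan says.** The abstract states: "Process and implementation evaluations are included and the study design includes a cost-utility analysis". The Cost-utility analysis section repeats the label: "The study was designed to conduct a cost-utility analysis and includes estimates of the direct costs, per participant, of implementing the intervention". Its numerator has two parts, the resources used to deliver the programme and the resulting change in the organisation's care costs.

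On the instrument it says: "We have included the EQ-5D [65], a brief, self-administered, health-related quality of life measure". It adds that responses are commonly turned into an index that reflects the utility of a health state.

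Two kinds of ratio are then fixed. The first is "We will calculate incremental cost-effectiveness ratios for each intermediate trial outcome". For the second, the investigators "will further report such a ratio for the improvement in mean EQ-5D scores between the intervention and control groups". The article nowhere mentions QALYs, an area under the utility curve or a time horizon, and it does not name the visit at which the mean is taken.

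The section Assessment data collection and measurement places assessments at baseline, 6, 12 and 24 months. Of the self-reported measures it says: "These measures are shown in Table 1". Table 1, which is titled as the data collection schedule, has rows for the SF-36 general health subscale and the Wisconsin Quality of Life Index at all four visits. It has no EQ-5D row.

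**The concern.** A cost-utility ratio should compare cost and utility accumulated over the same period. Here the numerator accumulates and the denominator, as worded, does not. A gain of 0.04 that lasts a month and a gain of 0.04 that lasts two years give the same denominator if the score is read while both are present.

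The Methods/design section gives the purpose of this analysis as informing planners who are deciding whether to adopt the programme. They would normally set the result against other cost-per-QALY figures. A cost per EQ-5D point does not allow that comparison, although the label cost-utility invites it.

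The schedule adds a second difficulty. With no EQ-5D row in Table 1, a reader cannot tell which visits supply the mean, or whether there are enough visits to form QALYs.

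**Working it through.** **The section's own figure.** "Response patterns yield 243 unique health states". Five dimensions at three levels give 3^5 = 243, so this is right. It identifies the three-level version. The point does not turn on it.

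**Inputs from the documents.** Visits are at 0, 0.5, 1 and 2 years. The Power analysis of primary aims section gives the assumed weight losses, so the between-arm differences are:
- 6 months: 5.9 − 1.6 = 4.3 percentage points
- 12 months: 4.4 − 1.6 = 2.8
- 24 months: 3.6 − 1.8 = 1.8

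**Assumed inputs.** The article gives no cost or EQ-5D values. I assume an incremental cost of 1,000 units, held fixed across horizons, no baseline difference and no discounting. There are two EQ-5D patterns:
- Fading: a peak difference of 0.05 at 6 months that shrinks in the weight proportions, giving 0.05 × 2.8/4.3 = 0.0326 at 12 months and 0.05 × 1.8/4.3 = 0.0209 at 24 months.
- Constant: 0.04 at every follow-up visit.

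**Formulas.** Cost per point = cost ÷ difference at one visit. QALY gain = sum over intervals of (interval length) × (average of the two end differences).

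**QALY gains.**
- Fading, to 1 year: 0.5 × 0.05/2 + 0.5 × (0.05 + 0.0326)/2 = 0.0125 + 0.0206 = 0.0331.
- Fading, to 2 years: 0.0331 + 1 × (0.0326 + 0.0209)/2 = 0.0599 (unrounded inputs).
- Constant, to 1 year: 0.5 × 0.04/2 + 0.5 × 0.04 = 0.03.
- Constant, to 2 years: 0.03 + 1 × 0.04 = 0.07.

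| Pattern | Per point, 6 mo | Per point, 12 mo | Per point, 24 mo | Per QALY, 1 y | Per QALY, 2 y |
|---|---|---|---|---|---|
| Fading | 20,000 | 30,700 | 47,800 | 30,200 | 16,700 |
| Constant | 25,000 | 25,000 | 25,000 | 33,300 | 14,300 |

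**Reading the table.** Under fading, the spread across visits is 47,800 ÷ 20,000 = 2.4-fold. This is simply 4.3 ÷ 1.8, so it does not depend on the assumed cost or peak. Under a constant difference the spread disappears. The per-point ratio still does not equal cost per QALY at either horizon, because the QALY gain grows with time and the score difference does not.

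**The schedule.** The cost-utility text says EQ-5D was included and is self-administered. Table 1 is offered as the list of measures and visits and does not show it. The two need to be reconciled.

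**The case against.** The strongest reply is that the ratio does concern utility. The section describes the EQ-5D index as reflecting preference value, so cost divided by a difference in that index is cost per unit of utility. That stands. A reader might infer that the planned ratio is not a utility-based result at all, and the text does not support this. What is missing is duration.

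Second, the wording names no visit, so the mean could be read at one visit, averaged over visits or weighted by time, and a condensed article may leave such detail to a fuller plan. A time-weighted mean difference over exactly 12 months equals the QALY gain numerically. This stands in part: dependence on the visit is conditional on a single-visit reading and on a difference that changes over time. It does not rescue the stated denominator. Over 24 months the time-weighted mean is half the QALY gain (0.0599 ÷ 2 = 0.0299 under fading), so even that reading fails to give cost per QALY over full follow-up. The article also does more than stay silent, because it names a mean-score denominator.

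Third, a reader might infer from Table 1 that EQ-5D was never collected. The documents do not support that. The text says it was included, and Table 1 also lacks rows for smoking and for self-reported diabetes and hypertension, all of which are reported in Table 2. The missing row is a reporting inconsistency.

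Fourth, this analysis sits outside the primary aims, and ratios for the other outcomes are planned beside it. That is true and limits the consequence, but this is the only ratio that bears on utility.

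**Conclusion.** The concern holds in a limited form. The one utility-based ratio in an analysis labelled cost-utility has a denominator without duration that is not matched to the period of the costs. The result would be cost per unit of utility at an unstated time and would not be comparable with cost-per-QALY results. This rests on the wording alone and needs no assumed values.

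Dependence on the visit is conditional. It is about 2.4-fold if a single visit is used and EQ-5D fades as weight is assumed to, and it is absent if the difference is constant. A reader might go further and say that the ratio must swing several-fold, or that it becomes undefined by 24 months. The first needs assumed EQ-5D values. The second needs the 24-month visit to be the one used, which the article does not say, and cost per QALY is also unstable when its own gain is near zero. All monetary figures above are hypothetical.

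The Table 1 omission is a separate, smaller inconsistency. No effectiveness conclusion is affected. The change is worth making because the economic result is meant to guide adoption and the correction is cheap.

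**What to change.** Define the denominator of the utility ratio as the between-arm difference in QALYs. Compute it as the area under the EQ-5D index curve over the visits at which EQ-5D was collected, adjusted for the baseline index. State one time horizon and use it for both costs and QALYs. If EQ-5D was taken at only some visits, limit the horizon to those.

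If QALYs cannot be formed, relabel the ratio as cost-effectiveness per EQ-5D point and name the visit.

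In either case, add an EQ-5D row with its visits to Table 1.

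The cost is a change of wording and a little more analysis work, with no new data if EQ-5D was collected at the scheduled visits. The small downside is that QALYs draw on several visits, so missing EQ-5D values have to be handled.
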